### Randomisation, blinding and treatment allocation

Randomisation is conducted using random numbers. Using a computer program (Microsoft Excel, Microsoft Corporation), a team member who does not participate in recruiting patients generates an Excel sheet with numbers representing the three intervention groups (using the command ‘=RANDBETWEEN(1,3)’). The random allocation sequence assigns patients in equal proportions to one of the three intervention groups. In this sheet, the numbers are masked until a new patient is enrolled, which assures that members of the study team accountable for participant recruitment are blinded until patients’ consent. Patients are blinded about their study arm allocation until the first intervention time-point (T1). There is no further blinding of the study team.

### Statistical analysis

All characteristics collected in the study are described in detail using descriptive methods. Qualitative characteristics are indicated by absolute and relative frequencies. Quantitative characteristics are described using mean values, SD, median, minimum and maximum. Parametric analysis methods are used to evaluate the primary and secondary target variables. If assumptions for parametric tests are violated, appropriate non-parametric alternatives will be considered.

Situational anxiety as the primary outcome (measured using the STAI-state) is analysed using separate 3×2 mixed factorial analyses of variance (ANOVAs) for each of the two chemotherapy sessions, with the between-subject factor ‘intervention’ (VR vs music vs control) and the within-subject factors ‘time’ (before vs after intervention). A probability of error of α=0.05 is set. The unit of analysis is individual patients. Effect sizes will be reported using partial eta squared (η²) for ANOVA analyses. Cohen’s d is calculated for post-hoc comparisons when appropriate. The secondary outcome criteria are analysed exploratively, also using ANOVAs and post hoc tests as appropriate. There is no adjustment of the probability of error. The statistical analysis is carried out with the help of standard statistical software (SPSS V.29). Participants will be included in the statistical analysis if they have completed both assessment time points and received the intervention for a minimum of 10 min per session. Furthermore, the intervention must be administered in consecutive sessions as scheduled. Participants who do not meet these criteria will be classified as dropouts. Both an intention-to-treat analysis and a per-protocol analysis will be performed. The results will be compared and discussed.

The feasibility of the intervention will be evaluated based on multiple data sources. A descriptive analysis of the screening and recruitment data will provide insights into patient participation and reasons for non-participation. Additionally, feasibility will be assessed based on study staff documentation during data collection sessions, as well as recorded reasons for dropout, and potential side effects. Furthermore, the evaluation questionnaire, which includes both usability assessment and self-developed items, will be analysed. The participants’ comments in the free text fields of the evaluation questionnaire will be categorised based on their content into issues and suggestions for improvement.

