## Methods

### Study design

The ViSu study is a single-centre, three-arm, non-blinded, randomised, controlled trial designed to investigate the efficacy of a VR mindfulness intervention and a music intervention in patients with cancer undergoing chemotherapy at the Interdisciplinary Outpatient Chemotherapy Center (IAC), University Hospital Düsseldorf, Germany. Participants will be randomly assigned to one of three study arms: (a) an intervention group receiving a VR-based mindfulness task, (b) an intervention group listening to music and (c) a control group with no intervention. The study protocol was developed in accordance with the Standard Protocol Items: Recommendations for Interventional Trials reporting guidelines.^19^ The checklist can be found in online supplemental appendix A.

The primary objective is to compare the effectiveness of the two interventions against a control group in reducing patients’ anxiety during two consecutive chemotherapy sessions. To evaluate whether the active VR intervention leads to any training or habituation effects, each participant will take part in two intervention sessions. Data collection will be conducted at both time points. Due to individual differences in chemotherapy schedules, the exact duration of chemotherapy treatment may differ between participants.

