### Sample size

Based on previous literature, we estimate an effect size of 0.25. The G*Power V.3.1.9.7 software^48^ was employed to determine the requisite sample size. Assuming that the probability of error does not exceed α=0.05 and that the power (1−β) is at least 0.95, an analysis of variance with three groups and two time points with N=66 subjects can demonstrate an effect size of 0.25. Based on previous research projects, we calculate a drop-out rate of 20%, which increases the total sample size to N=82.

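### The primary outcome is tested in two separate session-wise ANOVAs with no rule for combining them, and neither can test the training or habituation question

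*Protocol article*

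**What the plan says.** Under Study design, the protocol article states the primary objective as comparing the two interventions with control in "reducing patients’ anxiety during two consecutive chemotherapy sessions". The same section gives the reason for having two sessions: "To evaluate whether the active VR intervention leads to any training or habituation effects, each participant will take part in two intervention sessions".

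Under Statistical analysis, STAI-state "is analysed using separate 3×2 mixed factorial analyses of variance (ANOVAs) for each of the two chemotherapy sessions". The between-subject factor is intervention (three arms), and the only other factor is given as "the within-subject factors ‘time’ (before vs after intervention"). Session is not a factor. On error control the section says "A probability of error of α=0.05 is set". After a sentence that makes the secondary outcomes exploratory, it adds "There is no adjustment of the probability of error".

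Under Sample size, the inputs are "Based on previous literature, we estimate an effect size of 0.25" and "Assuming that the probability of error does not exceed α=0.05 and that the power (1−β) is at least 0.95". They are applied to one ANOVA with three groups and two time points, giving N=66, raised to 82 for 20% dropout.

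**The concern.** There are two problems, and both lie in what the article fixes.

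First, one primary outcome yields two primary results, T1 and T2. The article does not rank the sessions, set an order of testing, or say whether one or both must be significant. If they disagree, no rule gives the trial's conclusion. A rule chosen after the results are seen cannot restore error control.

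Second, the reason given for the second session is a question about change between sessions. Two models that each see only one session cannot test it. The likely substitute is to note that one session is significant and the other is not. That is not a test of whether the effect changed.

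**Working it through.** **Inputs.** From Sample size: effect size 0.25 (taken as Cohen's f), alpha 0.05, power 0.95, k=3 groups, m=2 time points, N=66. From Statistical analysis: two such ANOVAs, one per session. Assumed, because the article gives neither: pre/post correlation within a session ρ=0.5 (sphericity is automatic with two time points), and correlation r between a patient's T1 and T2 change scores, varied from 0 to 0.9. Equal arms of 22 are used.

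**Step 1: reproduce the stated N.** For the group × time interaction:

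λ = f²·N·m/(1−ρ) = 0.0625 × 66 × 2 / 0.5 = 16.5, with df = 2 and 63.

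The noncentral F distribution gives power 0.953 at alpha 0.05, and 66 is the smallest multiple of three that reaches 0.95. With the same inputs the time main effect would need 57 and the group main effect 189. The figure of 66 is therefore the interaction test in one session, tested once at 0.05.

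**Step 2: either session counts as success.** Under independence the chance of at least one false positive is 1 − 0.95² = 0.0975. For correlated sessions, two F tests on change scores were simulated (3 × 22 patients, 200,000 runs per value of r).

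**Step 3: both sessions required.** The same simulation under the null gives the joint false-positive rate. Under a true effect of the planned size in both sessions (λ = 16.5 each) it gives joint power. With r=0 joint power can be checked directly: 0.953² = 0.909.

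| r | False positive, either session | False positive, both sessions | Power for both |
|---|---|---|---|
| 0 | 0.097 | 0.003 | 0.91 |
| 0.3 | 0.095 | 0.004 | 0.91 |
| 0.5 | 0.091 | 0.008 | 0.92 |
| 0.7 | 0.084 | 0.014 | 0.92 |
| 0.9 | 0.071 | 0.028 | 0.94 |

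The both-sessions false-positive rates hold when there is no effect in either session. If one session has a real effect and the other has none, the joint claim is still false in at most 5% of trials, because the null session must itself reach significance.

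**Step 4: split alpha.** At 0.025 per session, power at N=66 falls from 0.953 to 0.916. Restoring 0.95 needs 75 evaluable patients, or 75/0.8 = 93.75, so 94 enrolled.

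**Step 5: the session question.** Testing whether the effect changes between sessions requires an intervention × time × session term. Neither planned ANOVA has one, and the feasibility analyses described next do not compare sessions on STAI-state. The informal substitute misleads. With an identical true effect of the planned size in both sessions, the simulation found exactly one session significant in 9% of trials at r=0 and 4% at r=0.9.

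**Step 6: one averaged test.** If the effect is equal in both sessions, averaging the two change scores multiplies λ by 2/(1+r). At r=0.5, λ = 16.5 × 2/1.5 = 22 and power is 0.989. At r=0.9, λ = 17.4 and power is 0.962. If the effect appears in one session only, the average halves it and λ is multiplied by a further 1/4. At r=0.5, λ = 5.5 and power is 0.52.

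**The case against.** A reader might infer that the trial runs at nearly 10% type I error. The text does not support that as a flat statement. The inflation needs an either-session rule, which the article does not state, and an objective worded over two sessions can equally be read as requiring both. On that reading error is controlled and the cost falls on power. What stands is that the article does not choose.

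A reader might also take the no-adjustment sentence as an explicit waiver for the primary tests. It directly follows the sentence on exploratory secondary outcomes and probably refers to those. Even so, no other control is stated for the two primary ANOVAs.

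It is also tempting to call the T2 pre-to-post comparison invalid because the T2 pre-score follows the first intervention. That goes too far. The arms remain randomised, the contrast addresses a within-session effect, and with no effect in either session its error rate is unaffected.

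Finally, training or habituation is not labelled the primary objective, all four STAI-state scores are collected, and an analysis plan not shown could add a session comparison. So the question is answerable from the data. The point is narrower: the analysis that the article fixes does not match the reason it gives for the second session.

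**Conclusion.** The point holds in two parts.

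The primary claim lacks a decision rule. The nominal 5% is exceeded (about 7% to 10%) if either session suffices. If both are required, joint power is about 91% to 94%, below the 95% planned for the one test that was sized. These figures assume f=0.25 in each session where power is concerned, ρ=0.5, equal arms, and r between 0 and 0.9. The direction does not depend on where r falls in that range.

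The training or habituation question has no test in the stated analysis, whatever values are assumed.

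**What to change.** Replace the two ANOVAs with one model on all four STAI-state scores: intervention × time (pre/post) × session, as a 3×2×2 mixed ANOVA or the equivalent linear mixed model with patient random effects. Then state that:

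- the intervention × time effect averaged over both sessions is the single primary test at 0.05, with pairwise arm comparisons only if it is significant;
- intervention × time × session is the prespecified training/habituation test;
- session-specific results are secondary;
- the no-adjustment sentence applies to secondary outcomes only.

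A model of post-scores alone, adjusted for the T1 pre-score, is not recommended. Its arm × session term would mix a lower T2 starting level with a change in the within-session effect. Also, under Recruitment and participant timeline, allocation is disclosed at T1 when the preintervention questionnaire is given, so that covariate may already reflect the arm.

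Minimal alternative: keep the two ANOVAs, test each at 0.025, restate power as about 92% at N=66 (assuming ρ=0.5), and add the intervention × time × session test.

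The cost is a change to the primary-analysis wording, using the same data and software. It should be made before outcome data are analysed by arm. The averaged test loses power if the effect is confined to one session (0.52 at r=0.5), which the sponsor should accept knowingly. The trial was not sized for the three-way term, so its estimate should be reported with a confidence interval.

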### Measures

Patients complete four different types of questionnaires during their study participation at the following measurement time points: after recruitment (T0; baseline), before the intervention (preintervention), after the intervention (postintervention) and at the end of the study (evaluation). All questionnaires were used in the German version. Additionally, physiological parameters (heart rate and blood pressure) are measured during the intervention phase. The preintervention, during-intervention and postintervention measurements are administered two times over two consecutive chemotherapy sessions (T1 and T2). Table 2 outlines the measures employed and the corresponding time points at which they are collected. Furthermore, saliva samples are collected both before and 25 min after the intervention, while heart rate and blood pressure are recorded at 5-minute intervals during the intervention. A detailed presentation of all measures used in the study is described in the following sections.

**Table 2 T2:** Overview of measures used for the study and the measurement time points

Measure	Baseline	Preintervention	During intervention	Postintervention	Evaluation
Demographic data	X				
Cancer-related data	X				
VAS-social support	X				
Previous experiences with mindfulness and music for relaxation	X				
ASKU	X				
PHQ-4	X	X			
STAI-trait	X				
Salivary cortisol		X		X	
STAI-state		X		X	
PA-F-KF		X		X	
MIDOS-2		X		X	
VAS-anxiety		X		X	
VAS-relaxation		X		X	
Heart rate			X		
Blood pressure			X		
VAS-tolerability of chemotherapy				X	
VAS-perceived duration of chemotherapy				X	
PSSUQ*					X
VR-specific evaluation (self-developed)*					X
Music-specific evaluation (self-developed)†					X

* VR group only

† Music group only

ASKU, Short Scale for Measuring General Self-efficacy Beliefs; MIDOS-2, Minimal Documentation System version 2; PA-F-KF, Fear of Progression Questionnaire Short Form; PHQ-4, Patient Health Questionnaire-4; PSSUQ, Post-study System Usability Questionnaire; STAI, State-Trait Anxiety Inventory; VAS, Visual Analogue Scale; VR, virtual reality.

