### Primary outcome measure

#### State-Trait Anxiety Inventory (STAI-state)

The STAI^36^ is a self-report questionnaire that can assess both situational state-anxiety and stable trait-anxiety. The short version with 10 items was used to assess the situational state-anxiety as the primary outcome.^36^ The response for each of the 10 items is based on an 8-point Likert scale (1=‘not at all’; 8=‘completely’). Four items need to be inverted before calculating the total score. The STAI-state score ranges between 10 and 80. Higher values indicate higher state-anxiety. The STAI reveals excellent internal consistency of α=0.90.^36^

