**Figure 2 F2:**
[figure not shown]
Participant timeline. VR, virtual reality.

The study team screens for general anxiety symptoms using the GAD-7 questionnaire.^20 21^ To ensure that participants are experiencing a level of anxiety significant enough to benefit from the interventions and demonstrate measurable changes in the primary outcome variable, only patients with at least moderate anxiety (defined as a score ≥5) are included in the study. Patients are randomly assigned to one of three intervention arms using computer-generated random numbers; however, they remain blinded to their group allocation until the first intervention time point (T1).

After recruitment, participants complete the first questionnaire for baseline assessment (T0). The intervention begins during the subsequent chemotherapy session at the IAC (T1). At this point, patients are informed of their study allocation and receive the preintervention questionnaire. Following the completion of the questionnaires, and after the flushing and premedication processes as part of the chemotherapy session, patients provide the first saliva sample by insalivating a cotton swab. The study team then assists patients in initiating the intervention.

Patients in intervention group 1 wear a VR headset and headphones and begin the mindfulness exercise. Patients in intervention group 2 put on headphones and listen to music. Patients in the control group 3 receive no additional treatment. A member of the study team remains with the patient, collecting data on heart rate and blood pressure at 5-minute intervals. After approximately 15–20 min, the intervention concludes. Patients then complete the postintervention questionnaire, and a second saliva sample is collected after 25 min. This procedure is repeated during the subsequent chemotherapy session (T2). Finally, patients in all groups receive a questionnaire specifically evaluating the intervention immediately after the second measurement time point. Participants in groups 2 and 3 are given the opportunity to try the VR intervention independently of data collection.

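### The before/after ANOVA for STAI-state is valid but is a change-score test; for session 1, adjusting the post score for the pre score already collected is in expectation more precise

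*Protocol article*

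**What the plan says.** Under Statistical analysis, the protocol article states that situational anxiety "is analysed using separate 3×2 mixed factorial analyses of variance (ANOVAs) for each of the two chemotherapy sessions". The between-subject factor is arm, set out as ("VR vs music vs control) and the within-subject factors"; the within-subject factor is "time’ (before vs after intervention"). No covariate is named, and "A probability of error of α=0.05 is set".

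The outcome is the STAI-state: "The short version with 10 items was used to assess the situational state-anxiety as the primary outcome", scored 10 to 80. Under Measures, the pre- and post-intervention "measurements are administered two times over two consecutive chemotherapy sessions (T1 and T2"). A pre score therefore exists for each session.

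Two timing facts matter. Under Recruitment and participant timeline, for T1: "At this point, patients are informed of their study allocation and receive the preintervention questionnaire". The T2 pre score is taken at the next chemotherapy session, after the T1 intervention.

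Under Sample size: "Based on previous literature, we estimate an effect size of 0.25", with α = 0.05, power of at least 0.95, three groups and two time points. This gives N = 66, raised to 82 for 20% dropout.

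**The concern.** A mixed ANOVA with two time points tests arm-by-time by comparing mean change between arms. It fixes the coefficient of the pre score at 1, whereas ANCOVA estimates that coefficient from the data. When the pre–post correlation is moderate, fixing it at 1 adds noise.

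This matters because the trial is small, at about 22 evaluable patients per arm. Allocation is by unrestricted random numbers, so chance differences in the pre score are to be expected. A chance imbalance d leaves a conditional error of (1−ρ)d in the change-score estimate, in absolute size, and ANCOVA removes it in expectation. At stake is precision in the session-1 comparison, obtainable from data already collected.

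**Working it through.** **Inputs.** From the article: 3 groups, 2 time points, effect size 0.25 (read here as Cohen's f), α = 0.05, power 0.95, N = 66. Assumed: ρ, which the article does not give; equal arms of 22; a common SD s.

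**Reproducing N = 66.** For the arm-by-time interaction the noncentrality is λ = f²·N·m/(1−ρ), with m = 2 time points. The degrees of freedom are (3−1)(2−1) = 2 and (N−3)(2−1) = 63. At ρ = 0.5, λ = 0.0625 × 66 × 2 / 0.5 = 16.5 and power is 0.953. N = 66 is the smallest multiple of 3 that reaches 0.95. With the same inputs, the within-subject test gives 57, the between-subject test 189 and a one-way ANOVA 252. The sample size thus matches the interaction, which is the change-score test. With dropout, 66/0.80 = 82.5, consistent with the stated 82.

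**Precision at T1.**
- Change score: variance 2s²(1−ρ).
- ANCOVA: variance s²(1−ρ²).
- Ratio: (1−ρ²)/[2(1−ρ)] = (1+ρ)/2.
- Estimating the slope multiplies this by about 1 + 1/(66−3−2) = 1 + 1/61.

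| Assumed ρ | Variance ratio | SE ratio after slope cost |
|---|---|---|
| 0.3 | 0.65 | 0.813 |
| 0.5 | 0.75 | 0.873 |
| 0.7 | 0.85 | 0.929 |
| 0.9 | 0.95 | 0.983 |

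Break-even is where (1+ρ)/2 × (1 + 1/61) = 1, so ρ ≈ 0.97. In simulation (4,000 replicates, N = 66, SD 1), the SE of a pairwise contrast was 0.303 for change against 0.263 for ANCOVA at ρ = 0.5, 0.236 against 0.220 at 0.7, and 0.133 against 0.131 at 0.9. ANCOVA had the smaller estimated SE in 99%, 96% and 67% of simulated trials respectively.

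**Omnibus power at ρ = 0.5.** λ becomes 16.5/0.75 = 22 with 2 and 62 degrees of freedom, and power is 0.989 (0.988 if λ is also reduced for the slope cost). In sample-size terms, 66/0.75 = 88 patients analysed by change scores would give the same variance.

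**Pairwise illustration, VR against music (ρ = 0.5, 22 per arm, f = 0.25).** The result depends on where the music arm is assumed to lie:

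| Music effect as share of VR effect | Power, change score | Power, ANCOVA |
|---|---|---|
| 25% | 82% | 91% |
| 50% | 51% | 63% |
| 75% | 16% | 20% |

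**Disclosure at T1.** Suppose disclosure shifts the pre score by d = −0.3 SD in one arm, with ρ = 0.6 and no in-session effect.
- Only the pre score moves: the change score errs by 0.30 and ANCOVA by 0.6 × 0.30 = 0.18.
- Pre and post move alike: the change score errs by 0 and ANCOVA by (1−0.6) × 0.30 = 0.12.

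**Session 2.** Adjusting the T2 post score for the T1 pre score gives variance s²(1−r²), where r is the correlation across sessions. The within-session change score has 2s²(1−ρ). With assumed ρ = 0.7 and r = 0.5 this is 0.75s² against 0.60s², so ANCOVA is 25% worse. With 0.8 and 0.6 it is 0.64s² against 0.40s², 60% worse. ANCOVA gains only if r exceeds √(2ρ−1), which is 0.63 at ρ = 0.7.

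**The case against.** The strongest reply is that nothing in the plan is wrong: the 3×2 ANOVA is a legitimate randomised comparison, and choosing ANCOVA is a preference about efficiency. That stands, and the point claims no more. A reader might infer that the planned test is invalid, or that it carries a chance imbalance wholly into the result. Neither follows: the test is valid, and the conditional error from a chance imbalance is (1−ρ)d.

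The second reply is that the gain may be small. Pre and post are completed in one sitting, so ρ could be high. At 0.9 the SE falls by only about 2%, and above about 0.97 ANCOVA loses slightly. This stands too, so it would be too strong to say that ANCOVA is never less precise or comes at no cost.

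Third, the T1 pre score is not a clean baseline, since patients learn their arm at the point where they receive the questionnaire. This stands as a caveat and cuts both ways, as the two disclosure cases show. It is a reason to report both analyses, and does not by itself favour change scores.

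Fourth, the argument does not carry over to session 2. This stands. Adjusting for the T1 pre score changes the target to the cumulative effect since T1 and may lose precision. The T2 pre score may already reflect the T1 intervention, so adjusting for it is not baseline adjustment.

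Finally, a rise in VR-against-music power from 51% to 63% might be read as the result. It assumes that music lies exactly midway between VR and control; the Introduction gives only an ordering.

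**Conclusion.** The point holds as an efficiency recommendation for session 1. The planned interaction test is a change-score analysis, and an ANCOVA on the T1 pre score has, in expectation, a variance smaller by a factor of about (1+ρ)/2, at the price of one degree of freedom. At ρ = 0.5 that is about 25% less variance, an SE about 13% smaller, and omnibus power of about 0.989 instead of 0.953. The size rests on an assumed ρ, equal arms, a common SD, and 0.25 being Cohen's f. The precision formula also treats the pre score as a baseline unaffected by allocation, which disclosure at T1 puts in some doubt. For session 2 the documents do not support replacing the planned within-session analysis.

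**What to change.** **Session 1 (T1).** Make the primary test an ANCOVA of post-intervention STAI-state on arm, adjusted for the T1 pre-intervention STAI-state and optionally for the T0 STAI-trait. Report adjusted pairwise differences in STAI points with 95% confidence intervals. Keep the 3×2 ANOVA as a sensitivity analysis, and say that it is there because disclosure may have moved the pre score.

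**Session 2 (T2).** Keep the planned within-session change analysis as the in-session comparison. If a model adjusted for the T1 pre score is added, state that it estimates the cumulative effect and may be less precise than the change score. Do not describe adjustment for the T2 pre score as baseline adjustment.

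**Reporting.** State the ρ assumed. Give any pairwise power figures only as an illustration, with the assumed position of the music arm.

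**Cost.** No new data, one covariate in SPSS and one degree of freedom. Because this replaces the published primary model of a non-blinded trial, it needs a dated and documented amendment, made before STAI-state is compared between arms. If that comparison has already been made, keep the planned ANOVA as primary and report the ANCOVA as supplementary.

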### Data monitoring and management

A randomisation file will be used to allocate a participant code to the intervention arms. A recruitment file is used to allocate the participant code to all included patients and, further, contains patients’ diagnoses, medical clearance and information about the recruitment process (treating physicians’ approval for study participation, checklist for how many attempts were needed to meet the patient in the IAC, date of informed consent). A data file contains pseudonymised survey data of patients for each measurement time point. Another file will be used to anonymously assess drop-outs, screening failures and reasons for non-participation or lack of interest. The data will be entered by the study team accountable for implementation of the study and will be double-checked by another team member. Supervision by the study team during chemotherapy sessions ensures the questionnaires are fully completed by participants. Data records will be kept separate from the consent forms. Data records of patients who did not meet the inclusion criteria (screening failures) will be disposed of in accordance with data protection regulations. After collection, salivary cortisol samples will be temporarily stored in a freezer (−20°C) and sent to a laboratory (Dresden LabService GmbH, Technical University of Dresden, Germany). Questionnaires and cortisol levels derived from saliva samples will be stored as combined research data for at least 10 years (in accordance with the principles of Good Clinical Practice). Access to the anonymised final trial dataset will be granted on request to the study team; the intended use of the data must be disclosed, after which the appropriate dataset will be provided.

Patients will receive standard medical care during the whole participation. No adverse side effects are expected due to the interventions and participating patients do not face higher risks compared with patients who are not participating in the current study. As a member of the study team will supervise each session, participants can terminate the intervention at any time. Participants can report any side effects to the study team and use the evaluation questionnaires for thorough feedback. Therefore, study monitoring is not needed.

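### The entry rule for the statistical analysis is a completer-and-exposure rule that contradicts the promised intention-to-treat analysis, and its 10-minute criterion has no counterpart in the control arm

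*Protocol article*

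**What the plan says.** All of the following is in the protocol article.

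- **Entry rule (Statistical analysis).** "Participants will be included in the statistical analysis if they have completed both assessment time points and received the intervention for a minimum". That minimum is set at 10 min in each session. In addition, "the intervention must be administered in consecutive sessions as scheduled". Then: "Participants who do not meet these criteria will be classified as dropouts". Nothing limits these sentences to one of the analysis sets.
- **Promised analyses (same paragraph).** "Both an intention-to-treat analysis and a per-protocol analysis will be performed". The two sets of results are to be compared and discussed. Neither set is defined under its own name and neither is called primary.
- **Primary analysis (same section).** STAI-state is analysed by a 3×2 mixed ANOVA (arm by before/after), run separately for each of the two chemotherapy sessions.
- **Control arm.** Study design describes "a control group with no intervention". Recruitment and participant timeline says "Patients in the control group 3 receive no additional treatment".
- **Early stopping.** Data monitoring and management allows participants to end the intervention whenever they wish. Risk to patients lists cybersickness, raised stress or anxiety and a feeling of lost control as possible risks, chiefly with VR.

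**The concern.** An intention-to-treat analysis keeps patients in the arm to which they were randomised, whatever exposure they had. A rule that admits only adequately exposed completers to the analysis cannot stand beside it. An analyst following the paragraph literally would run a selected comparison and could still believe that the intention-to-treat promise had been kept.

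The selection is also not the same in each arm. "received the intervention for a minimum of 10 min per session" describes something that a control patient cannot do or fail to do. The primary objective compares each intervention with control, and the outcome is state anxiety measured just after the intervention. If patients who remove the headset or headphones before minute 10 tend to be those who became more anxious, removing them flatters the interventions.

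A second loss is unnecessary. A patient with complete before and after scores at T1 who misses T2 is barred from a T1 ANOVA that uses no T2 data.

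**Working it through.** **1. The entry rule criterion by criterion**

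| Criterion | VR | Music | Control |
|---|---|---|---|
| Both time points completed | can exclude | can exclude | can exclude |
| At least 10 min of intervention per session | can exclude | can exclude | no meaning: no intervention is given |
| Consecutive sessions as scheduled | can exclude | can exclude | can exclude, if read as attendance |

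Taken literally, the second row leaves no control patient to analyse. If it is waived for controls, it acts on VR and music alone. The terminations listed under Sample (physical weakness, acute side effects or allergic reactions, progression, interrupted chemotherapy) apply to all arms.

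**2. The plan's own sample size, to fix the N used below**

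Inputs from Sample size: effect size 0.25 (taken as Cohen's f), α = 0.05, power 0.95, three groups, two time points. Assumed, because the article does not give them: correlation ρ = 0.5 between the two time points, and sphericity.

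For the group-by-time interaction, λ = f²·N·m/(1−ρ) with m = 2 time points, on 2 and N−3 degrees of freedom.

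- N = 66: λ = 0.0625 × 66 × 2 / 0.5 = 16.5; power 0.9535.
- N = 63: power 0.9436.

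So 66 is the smallest multiple of three that reaches 0.95, and the stated figure reproduces. Drop-out: 66/0.8 = 82.5, against the stated 82. The sample size is not in dispute here. With 20% lost, 82 × 0.8 = 65.6, so about 66 patients would remain under the entry rule.

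**3. How far one-sided exclusion could move the test**

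The article gives no early-stopping rate and no outcome for early stoppers, so every input here is an assumption. Let a fraction p of one active arm stop early, with an anxiety change w SD worse than that of the retained patients. The full-arm mean is the retained mean plus p·w, so excluding the stoppers shifts the arm by p·w towards benefit.

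- p = 10%, w = 0.5: shift 0.05 SD
- p = 10%, w = 1.0, or p = 20%, w = 0.5: shift 0.10 SD
- p = 20%, w = 1.0: shift 0.20 SD

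With no true effect and a shift d in one of three equal arms, f = d·√2/3 and λ = f²·66, with F on 2 and 63 degrees of freedom:

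| Shift d (SD of change) | f | λ | Type I error |
|---|---|---|---|
| 0 | 0 | 0 | 5.0% |
| 0.05 | 0.024 | 0.037 | 5.3% |
| 0.10 | 0.047 | 0.147 | 6.1% |
| 0.20 | 0.094 | 0.587 | 9.5% |

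**4. Cross-check with both active arms affected**

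This is a simulation with no true effect, 27 per arm, a fraction q of each active arm excluded, nobody excluded from control, and correlation r between the tendency to stop and a worse change. The spurious benefit is r·φ(z)/(1−q), where z is the upper-q normal quantile.

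- q = 10%, r = 0.3: 0.06 SD, type I error 5.3%
- q = 20%, r = 0.5: 0.175 SD, type I error 9.1%
- q = 30%, r = 0.5: 0.25 SD, type I error 13.0%; this exclusion fraction is above the plan's overall drop-out allowance
- r = 0: no shift, type I error about 5% at each q

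**The case against.** The best defence is that the sentence is a misplaced per-protocol definition. A per-protocol analysis needs such a rule, the paragraph offers no other, and the promise of both analyses follows directly. That may well be what was meant. But the text sets the rule for the analysis as a whole, and even as a per-protocol definition the 10-minute criterion still has nothing to match it in the control arm. Full set definitions and the choice of primary set are often left to an analysis plan that is not shown, so the missing ranking would be weak as a separate point. It matters here because the article does state a rule, and states it in conflict with intention-to-treat.

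A reader might also infer several stronger things that the article does not support:

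- **That all exclusions fall on the active arms.** Only the 10-minute criterion is arm-specific.
- **That bias is shown.** Nothing in the article says that early stoppers fare worse. Risk to patients lists possible risks, Data monitoring and management expects no adverse effects, and exclusion requires stopping before minute 10 of an exercise of about 15 min.
- **That 9.5% is the expected error rate.** It is the top of an assumed range and needs 20% early stopping in one arm with a change a full SD worse. The planned 20% is overall drop-out, not early stopping of VR.
- **That drop-outs cannot be traced to their arm.** The article does say "Another file will be used to anonymously assess drop-outs, screening failures and reasons for non-participation", but the randomisation file links participant code to arm and the survey data are pseudonymised, so arm and collected STAI scores remain linkable. At most, the recorded reasons lose their link.
- **That the mixed ANOVA is invalid.** Before and after scores come from the same supervised session, so complete pairs are a reasonable expectation.
- **That the more favourable result will be headlined.** The article says that both will be compared and discussed.

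**Conclusion.** The contradiction is in the text and holds whatever the size of any bias: one paragraph restricts the whole analysis to exposed completers and also promises intention-to-treat. The 10-minute criterion is undefined for controls, and the both-sessions criterion discards complete T1 data that the T1 ANOVA could use. With the planned 20% drop-out, up to about 16 of 82 patients (0.20 × 82 = 16.4) could be excluded. How many of them would have usable T1 data is not known, and this is not a count of biased exclusions.

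Bias towards the interventions is conditional. It needs early stopping to be related to a worse anxiety change, which is plausible from the listed risks but not quantified. Under assumed one-arm shifts of 0.05 to 0.20 SD, the type I error at N=66 is about 5.3% to 9.5%; with no such relation there is no bias. Because the rule decides who enters the primary randomised comparison, it should be corrected before the data are analysed.

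**What to change.** Change the Statistical analysis section as follows.

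- State that the primary analysis is intention-to-treat: all randomised patients in their allocated arm, using all available STAI-state data for each session, whatever the minutes of exposure and whether or not T2 was completed.
- Confine the 10-minute, both-sessions and consecutive-sessions rule to a per-protocol set, labelled as a sensitivity analysis.
- Give controls an equivalent observation-time criterion for that set. The structured documentation form described under Implementation and quality assurance already records start and end times, so this should need little new data collection.
- Report exclusions from each set by arm.

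A likelihood-based mixed model is one optional way to use every available value and could be fitted with the MIXED procedure in the SPSS software already named; the correction does not depend on it.

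The cost is mainly wording. The estimated effect may be slightly smaller, because patients with little exposure stay in their arm.
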